### The importance of psychosocial predictors of return to work

There is a paucity of information on potentially modifiable psychosocial predictors of return to work after stroke, especially in comparison with other cardiovascular diseases.[12] Studies of return to work following myocardial infarction have consistently found that psychosocial factors are important predictors.[11] In contrast, psychosocial factors have been considered in only a few stroke studies, where white collar workers[13] and those with higher education levels were found to be more likely to return to work in general,[11] and those with less demanding roles more likely to return after adjusting for stroke severity.[14] The most consistent predictors of return to work after stroke have been stroke severity (not modifiable) and dependency in activities of daily living (ADL).[11]

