## Methods/design

### Design and overview

POISE is a prospective multicentre observational study with study registration number ACTRN12608000459325. The primary aim of POISE is to determine if modifiable early (within 28 days of stroke) psychosocial factors are associated with people's ability to return to work one year after stroke. The secondary aim is to determine the economic impact of not returning to work for younger stroke survivors and their families. Participants are recruited as soon as possible after stroke from the Stroke Services New South Wales (SSNSW) network. Stroke status is verified by the recruiting centre staff and baseline demographic and clinical data are collected. Interviews are conducted by centrally located trained interviews at 28 days, 6 and 12 months.

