### Statistical analysis

We will conduct a logistic regression model with 'returned to work' as a dichotomous response variable and a combination of *a priori *and univariately associated variables described in the 'assessments and data collection' as explanatory variables. The associations with the continuous outcome of the number of quality hours of work returned to will be modelled using linear regression.

The time of first return to work will be modelled by all the other explanatory variables using a Cox regression (survival analysis) model. These models will be fitted on two subsets of data: paid and unpaid work. The same predictor variables will be tested in each model and coefficients in the models for paid and unpaid work will be compared in relation to their size and significance to see how different variables affect return to paid and unpaid work, and time to return to paid and unpaid work.

Economic hardship will be constructed as a dichotomous variable where a reported inability to make any one of the payments posed to respondents will be classed as a case of economic hardship. A logistic regression model will be fitted to determine the extent to which variables affect the risk of this outcome as outlined above. Estimates of average production losses associated with cases of stroke, and stroke with depression as a complication, will be estimated based on an analysis of average amounts of time off work multiplied at the various rates for estimating production gains/losses outlined above. Adjustment for production losses caused by return to work at impaired capacity will be estimated. A sensitivity analysis will be conducted on this economic outcome involving the differing valuation methods and scenarios regarding the level of impairment and its impact on production.

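### The production-loss figure for stroke with depression names no adjustment for stroke severity or prior mood disorder; an adjusted difference should be added beside the averages

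*Protocol article*

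**What the plan says.** Under Design and overview, the article gives the secondary aim: "The secondary aim is to determine the economic impact of not returning to work for younger stroke survivors and their families". The Statistical analysis section turns part of this aim into two outputs, "Estimates of average production losses associated with cases of stroke, and stroke with depression as a complication". The method for the second is given in the same sentence: "stroke with depression as a complication, will be estimated based on an analysis of average amounts of time off work". In full, the losses "will be estimated based on an analysis of average amounts of time off work multiplied at the various rates for estimating production gains/losses outlined above".

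One adjustment is named: "Adjustment for production losses caused by return to work at impaired capacity will be estimated". The economic sensitivity analysis is described as "involving the differing valuation methods and scenarios regarding the level of impairment and its impact on production".

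The other outcomes in the same section get regression models. Return to work has a logistic model with a priori "and univariately associated variables described in the 'assessments and data collection' as explanatory variables". Hours of work have a linear model, time to first return a Cox model, and economic hardship a logistic model.

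On severity, the Background section on psychosocial predictors says: "The most consistent predictors of return to work after stroke have been stroke severity (not modifiable"), and pairs it with dependency in activities of daily living.

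**The concern.** A separate loss figure for survivors whose depression is called a complication of stroke invites the reader to set it against the figure for stroke and to take the gap as the cost of depression. Two features make that gap hard to interpret.

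- **Severity.** The article itself treats stroke severity as a consistent predictor of return to work. It also relies on an earlier cohort result for neurotic symptoms that was adjusted for severity (Australasian data). The study aims for a broad range of severity and allows proxy consent so that severe strokes are not left out. If depressed survivors have more severe strokes, part of their extra time off work belongs to severity.
- **Prior mood disorder.** Depression is defined under Assessments and data collection by a HADS depression score of 8 or more after stroke. That score cannot separate new depression from depression that was there before. Calling it a complication treats all of it as following the stroke.

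The named adjustment, for impaired capacity after return, is a costing step. Changing the valuation method or the impairment scenario would rescale a confounded gap but not remove it. At stake is a secondary economic result in a study meant to identify targets for intervention.

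**Working it through.** The article gives no production-loss figure, no time off work by depression status and no severity mix by depression status. There is therefore no stated figure to reproduce. The check has two parts.

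**1. Text.** For each outcome, the method named in Statistical analysis is:

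- return to work: logistic regression with explanatory variables
- hours of work: linear regression
- time to first return: Cox regression with explanatory variables
- economic hardship: logistic regression
- production loss: average time off work times a rate; adjustment for impaired capacity only

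The data needed to adjust are collected. Site co-ordinators record stroke subtype and severity after consent. Table 1 lists date of birth, sex, pre-stroke hours and occupation, and pre-stroke psychotropic medication and talking therapy.

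**2. Illustration of size.** Only the 25% prevalence of depression comes from the article (Statistical considerations). All other inputs are assumptions. Depression is given no true effect on time off work, so any gap is due to severity. Let s be the share of severe strokes and d the proportion depressed among them.

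- Severe share among the depressed = s × d / 0.25
- Severe share among the others = s × (1 − d) / 0.75
- Apparent gap = difference in severe shares × (mean time off if severe − mean time off if not)

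Main case: s = 30%, d = 40%, time off 9 vs 5 months. Depression among non-severe strokes is then (0.25 − 0.12)/0.70 = 19%.

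- Depressed: 0.30 × 0.40/0.25 = 0.48
- Others: 0.30 × 0.60/0.75 = 0.24
- Gap: 0.24 × 4 = 0.96 months, or 0.96/12 = 8% of a year

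Lower case: s = 30%, d = 35%, 8 vs 5 months.

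- 0.42 − 0.26 = 0.16; 0.16 × 3 = 0.48 months, or 4% of a year

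Higher case: s = 40%, d = 35%, 10 vs 4 months.

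- 0.56 − 0.347 = 0.213; 0.213 × 6 = 1.28 months, or 11% of a year

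Balanced case: equal severe shares give a gap of 0 whatever the means.

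A second set of assumptions, stated directly as severe shares, shows how far the answer depends on the inputs. With mean time off of 20 weeks (mild) and 44 weeks (severe):

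- shares 40% vs 30%: 0.10 × 24 = 2.4 weeks
- shares 50% vs 30%: 0.20 × 24 = 4.8 weeks
- shares 60% vs 25%: 0.35 × 24 = 8.4 weeks

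With means from 25/40 to 15/48 weeks and the same three pairs of shares, the range is 0.10 × 15 = 1.5 to 0.35 × 33 = 11.6 weeks. In this additive set-up the error is the same when depression does have an effect: with a true effect of 6 weeks, 2.4 weeks of bias gives an apparent 8.4.

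These gaps compare depressed with non-depressed survivors. The article does not say whether the stroke figure covers all cases or only those without depression. If it covers all cases, each gap shrinks by the factor 0.75 at 25% prevalence, so the main case becomes 0.72 months.

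No size was worked out for prior mood disorder.

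**The case against.** The strongest reply is that this is a condensed article. The text does not call the averages crude, and an analysis of average time off work could use adjusted or stratified means. The rates said to be outlined above do not appear earlier in the article as shown, so fuller economic methods may exist elsewhere. The wording is that of association, and no excess or attributable share is planned. An average loss per case type is a legitimate descriptive cost figure. The effect of depression on return to work is already to be studied with regression.

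Much of this stands, and it rules out stronger readings that a reader might infer:

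- *That the averages are certainly crude, or that losses will be credited to depression.* The article says neither.
- *That the figure is meant to show what treating depression would save.* The secondary aim concerns the impact of not returning to work and mentions neither depression nor treatment.
- *That severity is the strongest driver.* The article lists it among the most consistent predictors, together with dependency.
- *That a bias of known size exists.* No document input gives the link between severity and depression.
- *That the plan wrongly truncates time off at 12 months.* Twelve months is the last assessment, and no rule for non-returners is stated.

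What does not fall away is that the article is not silent on this estimate. It names a method, an adjustment and a sensitivity analysis, and none of them deals with severity or mood history. The planned regressions concern return to work, hours, time to return and hardship; none yields an adjusted production loss.

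**Conclusion.** The point holds in conditional form. The plan sets out a depression-specific production loss without naming any adjustment for stroke severity or pre-stroke mood disorder. If the averages are unadjusted, and those factors are more common among the depressed, comparing the two figures may overstate the loss linked to depression. The size cannot be determined from the documents. It is zero with balanced severity, about 0.5 to 1.3 months (4% to 11% of a year) under the first set of assumed inputs, and 1.5 to 11.6 weeks under the second. These ranges show that the bias could matter and are not estimates of it. The primary aim is unaffected.

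**What to change.** Keep the average losses for each case type and label them descriptive. State whether the stroke figure includes survivors with depression.

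Add an adjusted comparison: model time lost or production loss on depression at 28 days, with stroke severity, age, sex, pre-stroke hours and occupation, and pre-stroke psychotropic use and talking therapy as covariates. Then standardise over the cohort to give one difference. Base any statement about depression-related loss on that difference, and label it as loss within the 12-month follow-up.

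If a fuller plan already specifies such an adjustment, a sentence pointing to it is enough.

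The cost is one extra model to specify and possibly a smaller headline figure. The covariates are already collected. Prior treatment is only a proxy for prior mood disorder, so some confounding may remain and should be acknowledged.

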### Ethical approval

Full ethical approval was received from the Human Research Ethics Committee (HREC) of the Sydney South West Area Health Service (SSWAHS) in May 2008: Protocol X08-0084, and from local institutional research governance offices for each clinical centre. Written informed consent is obtained for every participant. Proxy consent is permitted for patients unable to provide consent themselves to avoid exclusion of those patients with severe stroke.

## Discussion

This study addresses a key National Research Priority (ageing well, ageing productively) for a common disabling disease for young Australians. Support for those coping with the aftermath of stroke has been repeatedly stated as a major deficit of current stroke services, and a high priority for consumers. Research in the psychosocial aspects of stroke recovery fills a large gap identified by the National Stroke Foundation Rehabilitation and Recovery Guidelines[40] endorsed by the National Health and Medical Research Council of Australia in 2005.

It is anticipated that this study will, for the first time, reliably identify targets for early intervention and vocational rehabilitation strategies that will increase the proportion of younger stroke survivors who are able to return to a gainful work, here in Australia and internationally. Improving this outcome is considered of primary importance to younger stroke survivors, clinicians and policy makers and may have substantial economic benefits, quantified within this study, and direct implications for the long term psychosocial wellbeing of the many thousands of younger stroke survivors, and their families. An important feature of this study is the quantification of the social and economic consequences of stroke for the individual, society and the global economy, and identification of the key targets for intervention strategies to mitigate these effects.

This study has already generated academic and clinical interest, and support and involvement from health professionals and stroke survivors.

